The first major multi-centre international study of long term POCD in people aged 60 and over (The International Study of Postoperative Cognitive Dysfunction, ISPOCD1 study1) reported an incidence of POCD of 25% 1 week after surgery and 10% after 3 months, despite excluding people with any pre-existing level of cognitive impairment from the trial. Importantly, the degree of POCD identified was of sufficient magnitude to interfere with day-to-day activities, emphasising the clinical significance of the problem. Furthermore, patients aged 70 and over had twice the incidence of POCD at 3 months (14%) than those aged 60 to 69 (7%). There are very few studies in patients aged 70 or older, who are probably the highest risk group; and only a handful of studies with periods of follow-up longer than 3 months. In a 12 month study undertaken by our group (appendix 1), including 100 participants over the age of 70 undergoing elective orthopaedic surgery, only 45% regained their full level of pre-operative cognitive performance over the subsequent 12 months, even when excluding individuals who developed delirium. Furthermore, people >80 were four times less likely to regain their full level of cognitive functioning than individuals between the ages of 70 and 80, suggesting that the risk of POCD continues to escalate with advancing age even over the age of 70. In addition, specific persistent deficits of attention were evident, particularly the speed of performance on attentional tasks. It is clear from these studies that some level of cognitive impairment is extremely frequent after major surgical procedures, especially in the oldest age groups. Surprisingly, despite the high incidence rates, awareness is low amongst the medical community and amongst surgical patients; and patients are rarely informed of the risk of POCD preoperatively as part of the consent procedure1.

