**5. Retrospective analysis of data to assess the role of the above interventions**

Our group has recently completed a retrospective analysis of changes in rSO2 in 46 older patients (mean age 65) undergoing abdominal surgery using the SICO. Twenty three (50%) of the patients had a drop in rSO2 of at least 15% and this was associated with ongoing major blood loss and low Hb and HCT. These changes persisted, despite optimization of anaesthetic depth (using the BIS monitor), arterial oxygenation (using pulse oximetry) and circulatory status using CVP and BP. In all cases, the fall in rSO2 could only be reversed by blood transfusion and with conventional monitoring would have gone unnoticed. As mentioned above, previous studies in awake patients undergoing carotid endarterectomy under local anaesthesia have demonstrated that a fall in rSO2 of this magnitude is often associated with substantial cerebral dysfunction4. An initial hypothesis is that these previously undetected falls in rSO2 represent a major and potentially preventable risk factor for POCD. However, other workers have demonstrated that falls in rSO2 as a result of haemodilution are not necessarily mirrored by falls in jugular venous oxygen saturation (SjO2), a measure of **global** cerebral hypoxaemia17. This could either be due to a greater sensitivity of the SICO versus SjO2 to reflect localised cerebral hypoxaemia8.

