**8** **Methods** **Participants, Inclusion and exclusion criteria**:

*Randomized Controlled Trial (RCT)*

One hundred patients, 60 years of age and older, with an American Society of Anesthesiologists (ASA) classification of fitness of 3 or less, undergoing major elective abdominal or orthopaedic surgery under general anaesthesia at King’s College Hospital will participate in the study.

Inclusion criteria

(1)Patients over 60 years of age classified as ASA (American Society of Anesthesiologists) of three or less who were due to undergo major elective abdominal or orthopaedic surgery (2) Mini Mental State Examination (MMSE) score equal to or greater than 23. (3) Adequate English was a pre-requisite to enable consent and to undertake study assessments.

Exclusion criteria

(1) Unable to complete the outcome measures (2) A diagnosis of Alzheimer’s disease or other dementia (3) Individuals undergoing surgical procedures under regional anaesthetics.

Assessments

1/ Electrocardiography (ECG) and laboratory tests as clinically indicated.

2/ Cognitive evaluation: Global cognitive function (Cambridge Assessment for Mental Disorder in the Elderly, section B (CAMCOG-B - , Mini-Mental State Examination -MMSE), memory (CAMCOG memory subscale), executive function (Trail – Making task part A and B) and vigilance accuracy and vigilance reaction time from the Cognitive Drug Research battery as indices of attentional performance and cognitive processing speed pre-operatively, 1 week post surgery and 12 weeks post surgery.

Definitions of POCD and other criteria for cognitive dysfunction will be validated based upon an initial cohort study (appendix 1).

Randomisation

Participants will be randomized according torandomisation lists, stratified by age group (65 to 70, 70 to 75 and over 75) , which will be generated by the study statistician in the statistical program package R. Based upon the list, sealed envelopes containing the randomization codes will be delivered to the operating theatres, and an envelope selected randomly by the anaesthetist. The randomisation envelope will be opened only after the participant’s eligibility and willingness to participate are re-confirmed prior to surgery.

Blinding

The trial will be double blind with the patients, informants and researchers blind to treatment allocation.

Monitoring and Intervention

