A bispectral index (BIS) of the electroencephalogram will be used to monitor anaesthetic depth. The target BIS range will be 40-60 (±5).

During and until extubation after the procedure, rSO2 will be continuously monitored using SICO to enable interventions if regional cerebral saturations drop by more than 15% from baseline or to less than 50% intraoperatively, using the following algorithm

1. BP maintained within 10% of baseline value by giving fluids or inotropes to bring the value back to within these limits
2. SpO2 maintained above 95% by increasing the FIO2 to 50%
3. Maintain EtCO2 between 4·5 to 5·5%. avoiding excessive hypercarbia as well as hypocarbia.
4. If there is ongoing moderate to severe haemorrhage consider transfusion if the Hb level is less than 9g.dl-1

If all the above fail to correct a decline then increase the etCO2 to 6% and give 100% O2.

Intervention

In the intervention group the anaesthetist will have full access to the BIS and SICO data to optimize the depth of anesthesia and to identify and facilitate intervention to rectify cerebral oxygen desaturation. In the control group the BIS and SICO data will be collected, but the anaesthetist will be blind to the monitoring data.

Statistical methods

The study is powered as a pilot study. A cohort of 73 patients gives 80% power to the 5% level of significance to detect a between group difference of 0·33 SD. The goal is to enroll 100 participants to allow for drop-outs.

The primary efficacy population will be defined as all patients who were randomised to receive the intra-operative anesthetic intervention or treatment as usual and completed at least one follow-up assessment. Statistical analyses will be undertaken using the SPSS software, version 17.0 (SPSS, Chicago, IL, USA). Two-sided p values of less than 0·05 will be deemed to be statistically significant. A full statistical evaluation protocol will be developed by the study statistician.

Additional Objectives

Fifty age matched controls will be recruited in parallel, drawn from the spouses of people undergoing surgery. The pre-operative assessment will include a standardized evaluation to identify pre-existing delirium (Confusion Assessment Method CAM29) or significant cognitive impairment including MMSE <2530, and/or the presence of dementia (DSMIIIR criteria, American Psychiatric Association 1987). This will allow additional comparisons between post-operative patients and age matched controls to address hypotheses b-f.

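### Abdominal and orthopaedic surgery are pooled, but the randomisation lists are stratified by age only, so the surgery mix of the arms is left to chance

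*Protocol*

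**What the plan says.** Protocol section 8 (Methods) admits patients "undergoing major elective abdominal or orthopaedic surgery under general anaesthesia" to a single trial. It does not state the expected split between the two surgery types. Under Randomisation, the lists are "stratified by age group (65 to 70, 70 to 75 and over 75"; no other factor is named. The envelopes go to theatre, with "an envelope selected randomly by the anaesthetist". Neither the randomisation text nor the statistical text mentions surgery type, and the detailed analysis is left to a later statistical document.

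The supporting data on the two surgery types are as follows:
- **rSO2, abdominal.** In the group's own series of 46 abdominal patients (section 5), "Twenty three (50%) of the patients had a drop in rSO2 of at least 15% and this was associated with ongoing major blood loss". The 122-patient randomised oximetry study described in section 4 is also abdominal.
- **rSO2, orthopaedic.** No figure is given anywhere.
- **Cognition, group's own data.** The 12-month study described in section 3 is orthopaedic, "including 100 participants over the age of 70 undergoing elective orthopaedic surgery".
- **Cognition, other.** The 122-patient abdominal study reports MMSE decline in the first week. The incidence figures in section 3 pool non-cardiac surgery.

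**The concern.** The oximetry part of the intervention acts only when rSO2 falls by more than 15% from baseline or below 50%. The protocol links falls of that size to major blood loss in abdominal patients and gives no corresponding rate for orthopaedic patients. Surgery type may therefore affect how often that part of the intervention comes into play, and the protocol has nothing to show that it does not.

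In a trial of about 50 per arm, an unbalanced surgery mix can be large enough to need explaining when the results are read. Stratification is built into the lists and envelopes before the first patient. A later analysis plan can adjust for surgery type, but it cannot restore balance in the design.

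**Working it through.** **Inputs.** From the protocol: 100 enrolled, 73 in the sample-size statement, target difference 0.33 SD. Assumed, because not stated: 1:1 allocation, an abdominal share of 30% to 50%, and an effect of surgery type on the outcome of 0.2 to 0.8 SD.

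**The plan's own figure.** The protocol gives no figure for imbalance. The 0.33 SD serves here only as a yardstick. The statement "A cohort of 73 patients gives 80% power to the 5% level of significance to detect a between group difference of 0·33 SD" is not reproduced by a two-group formula: ((1.96 + 0.84)/0.33)² ≈ 72.1 gives 73 for a one-sample or paired comparison, whereas two groups need 2 × 72.1, or 145 per arm and 290 in total. That is a separate matter and does not affect this point.

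**Step 1: chance imbalance with no stratification by surgery.** With K abdominal patients among N, and n in one arm, the number x of abdominal patients in that arm is hypergeometric(N, K, n). The difference in mix is x/n − (K − x)/(N − n). Age strata are ignored.

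| N | K | n | SD of difference | P(≥10 points) | P(≥20 points) |
|---|---|---|---|---|---|
| 100 | 50 | 50 | 10.1 points | 0.317 | 0.071 |
| 100 | 30 | 50 | 9.2 points | 0.275 | 0.049 |
| 73 | 36 | 36 | 11.8 points | 0.353 | 0.103 |
| 73 | 22 | 36 | 10.8 points | 0.446 | 0.074 |

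The 10-point column is not smooth at N = 73 because only certain differences are possible. For K = 22, differences just above 10 points count; for K = 36, the nearest value (9.6 points) falls just short. A more lopsided mix lowers the risk: at N = 100 with a 20% share, the two probabilities are 0.211 and 0.023.

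**Step 2: effect on the estimate.** Shift in the unadjusted difference = imbalance × surgery effect. For 20 points:
- 0.20 × 0.2 SD = 0.04 SD, which is 12% of 0.33
- 0.20 × 0.5 SD = 0.10 SD, which is 30%
- 0.20 × 0.8 SD = 0.16 SD, which is 48%

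For 10 points the shifts are half as large, 0.02 to 0.08 SD. The standard error of the difference at 50 per arm is √(2/50) = 0.20 SD.

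**Step 3: what accounting for surgery type gains in power.** At a 50:50 mix, a surgery effect g removes g²/4 of the outcome variance. With 50 per arm and 0.33 SD, power is 37.8% without adjustment. It rises to 38.2% for g = 0.2 and 43.7% for g = 0.8.

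**Step 4: imbalance left after the proposed change.** Take four strata and permuted blocks of size b. If the last block of a stratum stops after m patients, the arm difference in that stratum has variance m(b − m)/(b − 1). Averaged over m = 0 to b − 1 this is (b + 1)/6: 0.83 for b = 4 and 1.17 for b = 6. At a 50:50 mix with 50 per arm, the SD of the difference in mix is about 0.5 × √(4 × 0.83)/50 = 1.8 points for b = 4, and 0.5 × √(4 × 1.17)/50 = 2.2 points for b = 6. The worst case for b = 4 is 2 × 2/50 = 8 points. This compares with an SD of about 10 points now.

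**The case against.** The case against is substantial, and most of it stands.

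- **Age is the documented prognostic factor.** The protocol cites 14% against 7% POCD at 3 months for patients of 70 and over against 60 to 69, and poorer recovery above 80. Choosing age for a study powered as a pilot is defensible. This is a reason to keep age, not a reason to leave surgery type out.
- **Randomisation without this factor is valid.** Chance imbalance is already allowed for in the error rate. Large imbalances are uncommon, the likely shifts are smaller than the standard error of 0.20 SD, and the gain in power is small. All of this stands and limits the weight of the point.
- **Adjustment and reporting by surgery type belong to the analysis plan.** That stands too; their absence from the protocol is not criticised here.
- **The remedy fails if envelopes are still picked at random.** Correct, so the fix has to change that step as well.

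Three stronger readings are tempting, but the document does not support them:
- **That the evidence for the two surgery types does not overlap.** The 122-patient study gives early MMSE results after abdominal surgery, and the main incidence figures pool non-cardiac procedures. Only the rSO2 evidence is confined to one of the enrolled types. Even there, section 4 argues that blood loss and fluid shifts in other surgery may produce similar falls.
- **That surgery type is a known determinant of cognitive course.** Nothing in the protocol compares cognition between the two types.
- **That a null result could not be told apart from an intervention seldom triggered in one type.** Stratifying does not change how often the algorithm is triggered. Oximetry data are collected in the control arm too, so desaturation can be tabulated by arm and surgery type under the present design. The intervention also includes BIS-guided depth of anaesthesia.

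**Conclusion.** The point holds as a modest design improvement. The protocol pools two surgery types and has rSO2 evidence for only one of them. It fixes age as the sole stratifier, although surgery type is known beforehand and is easy to balance.

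At 100 patients and an assumed 30–50% abdominal share, the chance of a difference in surgery mix of at least 10 points is about 28–32%, and of at least 20 points about 5–7%. At 73 patients the chance of at least 20 points is about 7–10%. What this does to the estimate rests wholly on an assumed surgery effect: over 0.2–0.8 SD, a 20-point imbalance moves the unadjusted difference by 0.04–0.16 SD. The loss is in precision and ease of interpretation. It is not bias, and the trial would not be invalid without the change. What justifies raising it now is that the change is cheap before the first patient and cannot be made afterwards.

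**What to change.** Generate the lists by surgery type (abdominal / orthopaedic) crossed with two age bands, under 70 and 70 and over, in permuted blocks of varying size. These bands cover everyone eligible. The present ones begin at 65 although entry is from 60, and they share the boundary at 70. Replace the random choice of envelope with numbered envelopes opened in list order within each stratum; otherwise blocking cannot secure balance on either factor.

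**Cost.** New lists from the study statistician, who already produces them in R, and relabelled envelope sets. There would be four strata instead of three, about 25 patients each on average at 100. No extra patients or procedures are needed. The downsides are some incomplete blocks and slight predictability for the anaesthetist who opens the envelopes, which varying block sizes limit.

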**Details of the proposed investigation**

1. **Title**: **A PROSPECTIVE, RANDOMIZED, CONTROLLED EVALUATION OF THE EFFECTS OF OPTIMISATION OF CEREBRAL OXYGENATION AND DEPTH OF ANAESTHESIA ON POSTOPERATIVE COGNITIVE DYSFUNCTION IN ELDERLY PATIENTS UNDERGOING MAJOR ORTHOPAEDIC AND ABDOMINAL SURGERY**

2. **Research objectives**: The current proposal will determine the frequency and importance of Post-Operative Cognitive Decline (POCD) in older people (over the age of 65), determine the subsequent incidence of Mild Cognitive Impairment and dementia and evaluate the role of key peri-operative intervention strategies and biological risk factors which will enable the development and implementation of preventative therapeutic strategies.

3. **Background**: Clinical experience has always suggested that older people often develop impairments of cognitive function after major surgical interventions. It is however only over the last decade that systematic studies have investigated the problem, coining the term Postoperative cognitive decline (POCD). This body of work has highlighted the frequency and importance of POCD, which has become increasingly recognized as a common and potentially handicapping outcome after a broad range of major surgical procedures. Although there is some variability between reports, probably reflecting the individual study definitions of POCD and the differing age range of participants, the mean reported incidence rates are 25% (range 7 - 55%) at 1 week post-operatively and 10% (range 7-15%) at 3 months post-operatively for non-cardiac procedures. These findings clearly indicate that POCD is a frequent and often persistent syndrome at all ages.

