44. [name] AJ, Keir G, Thompson EJ: A specific and sensitive ELISA for measuring S-100b in cerebrospinal fluid. J Immunol Methods 1997; 205: 35-41

DG 13 5 2006

**Appendix 1**: Data collected for a cohort study on Post Operative delirium (n=100) will be evaluated, to provide pilot data to enable optimization study criteria for POCD and other indices of cognitive dysfunction in the RCT. Age at surgery was a significant predictor of recovery to baseline MMSE (t = 2.3 p = 0.023), with an odds ratio of recovery >2 for the under 80’s. Simple Reaction Time (SRT) showed the lowest recovery rate, with only 45% of patients recovering to their pre-operative level within the follow up period of twelve months. Importantly, slower pre-operative SRT (t=4.1 p=<0.0001) and Choice Reaction Time (CRT) (t=3.7 p=<0.0001 ) were significant predictors of “non-recovery”.

Table 1: Recovery rates for Global Cognition and Attention

|  | Follow Up Visits | | | | |
| --- | --- | --- | --- | --- | --- |
| 3 Days | 7 Days | 3 Months | 6 Months | 12 Months |
| MMSE | 45 | 74 | 91 | 92 | 92 |
| SRT | 23 | 36 | 40 | 44 | 45 |
| CRT | 27 | 58 | 68 | 77 | 77 |

Patients recovered to baseline (%).

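### The randomisation age bands do not match the eligibility age: eligible patients aged 60 to 64 have no list, and a 70-year-old fits two

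*Protocol*

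**What the plan says.** Three statements in the protocol set an age range for the randomised trial, and they do not agree.

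- Section 8, Participants: "One hundred patients, 60 years of age and older". Inclusion criterion 1 in the same section has a slightly different limit: "Patients over 60 years of age classified as ASA".
- Section 8, Randomisation: the lists are "stratified by age group (65 to 70, 70 to 75 and over 75".
- Section 2, Research objectives: the aim concerns decline "in older people (over the age of 65". This fits the lower edge of the strata but not the eligibility text.

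The closing paragraph of section 6 gives a further figure and describes the population as people above 70.

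Section 8 also describes the mechanics. The statistician generates the lists in R, sealed envelopes go to theatre, the anaesthetist picks one, and it is opened only once eligibility and willingness have been confirmed again. No rule is given for a patient whose age falls outside the bands or on a shared limit.

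**The concern.** Stratified lists work only if each eligible patient belongs to exactly one stratum, so the bands must cover every eligible age and must not overlap. Here they appear to fail on both counts.

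Two things are at stake. The first is allocation: a patient with no list has to be placed by improvisation, and a patient with two lists is placed by whichever set of envelopes is picked up. The second is the record: if the stratum is undefined or arbitrary at randomisation, an analysis that uses the stratification factor has no reliable value for those patients. An analysis plan can define how to code them afterwards, but it cannot repair allocations already made without a rule.

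**Working it through.** No sample size, power or error rate enters this point, and there is no protocol figure to reproduce. The check is one of set membership.

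**Inputs.** Bands from section 8, Randomisation: 65–70, 70–75, above 75. Eligibility from section 8, Participants (60 and above) and inclusion criterion 1 (above 60).

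**Step 1: count the bands that contain each age.** Age is in completed years, with both ends of each band included.

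| Age | Eligible? | Bands matched |
|---|---|---|
| 60 | Yes by the Participants text; unclear under criterion 1 | 0 |
| 61–64 | Yes under both | 0 |
| 65–69 | Yes | 1 (65–70) |
| 70 | Yes | 2 (65–70 and 70–75) |
| 71–75 | Yes | 1 (70–75) |
| 76 and above | Yes | 1 (above 75) |

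Five single-year ages have no list (four if age 60 itself is not eligible), and one has two.

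**Step 2: try kinder readings of the limits.**

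- Upper limit excluded, so that the first two bands are 65–69 and 70–74: the overlap at 70 goes. If the last band still means 76 and above, age 75 now has no list; if it means 75 and above, that problem goes too. Ages 60–64 still have no list.
- Exact age instead of completed years: the overlap shrinks to the 70th birthday. Everyone from 60 up to 65 still has no list.

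The gap below 65 therefore does not depend on the reading. The overlap at 70 does, and the protocol does not say which reading applies.

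**Step 3: check a corrected set.** With a lower limit of 60 and bands 60–69, 70–75, 76 and over, each band starts one year after the previous one ends (69 then 70; 75 then 76). Every eligible age matches exactly one band, and there are still three strata.

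**The case against.** **It is a slip that the statistician will correct when building the lists.** That may happen, and it explains why the cost is small. It does not make the text right: the protocol states the bands, and they conflict with its own inclusion criterion. Nor is this detail left to a later analysis plan, since the lists have to exist before the first patient is randomised.

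**The error may lie in the eligibility age and not in the bands.** This stands. The objectives speak of people above 65, which agrees with the lowest band. The documents do not show which statement is intended, so the request is to reconcile them, not to extend the bands downwards regardless.

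**Concealment is not really threatened.** This largely stands. A reader might infer that the overlap lets theatre staff steer allocation. But the envelopes are sealed and opened only after eligibility is re-confirmed, so choosing between two of them does not reveal the arm, and the anaesthetist already picks the envelope under the stated procedure. What remains is the missing rule and the ambiguous stratum record.

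**The top band should separate the over-80s.** A reader might go further and argue that the bands are also wrong because they merge ages 76–80 with the over-80s, whom the protocol treats as highest risk. The documents do not support this as an error. Section 3 gives that label to "patients aged 70 or older, who are probably the highest risk group". It does report that "people >80 were four times less likely to regain their full level of cognitive functioning", "suggesting that the risk of POCD continues to escalate with advancing age even over the age of 70", and Appendix 1 gives an "odds ratio of recovery >2 for the under" 80s. These are findings from the group's own 100-patient cohort. They could motivate a cut at 80, but everyone above 75 falls in exactly one list, so the width of that band is a design choice. Any estimate of the chance imbalance in over-80s would need stratum sizes and balance within strata, and the protocol gives neither.

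**Conclusion.** The point holds in a limited form. The strata contradict the eligibility age in the same section: eligible patients aged 60 to 64 have no randomisation list, and on a plain completed-years reading a 70-year-old has two. For all other eligible ages the lists can be used as written, so it would be too strong to say that the stratification as a whole cannot be applied.

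The size is five uncovered single-year ages (four if age 60 is excluded) and one doubly covered age. The number of patients among the 100 cannot be derived, because no expected age distribution is given. Section 5 reports a mean age of 65 in the group's retrospective series of 46 abdominal patients. That suggests that patients under 65 could be more than a handful, but it does not give a count.

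The gap rests on no assumption beyond the stated eligibility. The overlap assumes completed years with both limits included. Sample size and power are unaffected. The text should be corrected before the lists are generated, because a rule that cannot place eligible patients is wrong as written.

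**What to change.** 1. Reconcile the lower age limit across the research objectives, the Participants paragraph, inclusion criterion 1 and the strata, including whether age 60 itself is eligible.
2. Restate the strata in completed years as contiguous, non-overlapping bands that start at the agreed limit and cover every eligible age. If the limit stays at 60, one set is 60–69, 70–75, 76 and over; if it changes, the first band starts at the new limit.
3. Generate the lists from these bands, label the envelopes to match, and use the same bands as the stratification factor in the analysis.

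The cost is one rewritten line, alignment of the age statements, and regeneration of the lists in R. The number of strata stays at three, and no patients or procedures are added.

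### The anaesthetist's random pick of an envelope breaks the order of the age-stratified list, and no stated step lets the allocation be audited

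*Protocol*

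**What the plan says.** All of this stands in Protocol section 8.

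- **Sequence.** The lists are "stratified by age group (65 to 70, 70 to 75 and over 75"). The statistician of the study makes them with R.
- **Device.** The "sealed envelopes containing the randomization codes will be delivered to the operating theatres". Nothing is said about numbering, opacity, separate sets per age group, order of use or a log.
- **Selection.** The protocol then has "an envelope selected randomly by the anaesthetist".
- **Timing.** One safeguard is added at this point: "The randomisation envelope will be opened only after the participant’s eligibility and willingness to participate are re-confirmed prior to surgery".
- **Who is blind.** Patients, informants and researchers are to be kept unaware of the arm. The anaesthetist is not on that list.
- **Delivery.** "In the intervention group the anaesthetist will have full access to the BIS and SICO data"; in the control group the anaesthetist does not see these data. The anaesthetist therefore knows the arm.
- **Size.** "The goal is to enroll 100 participants to allow for drop-outs".

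**The concern.** A pre-generated list does its work when its entries are used in order within each stratum. If the next assignment is whichever envelope comes to hand, the list fixes only what is in the stock and not who receives what. Two things are at stake.

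The first is **balance**. Any blocking is lost, and if the envelopes of the three age groups lie together, so is the stratification. Age matters for this outcome: section 3 cites a multi-centre study in which dysfunction at 3 months was 14% in patients aged 70 and over and 7% in those aged 60 to 69.

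The second, and weightier, is **concealment and auditability**. The person who picks is the unblinded clinician who manages the patient, works beside a stock of envelopes in theatre, and has no fixed next number. With numbered envelopes used in order, a skipped or replaced envelope leaves a gap. With a free pick there is no expected next envelope against which to check an assignment.

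**Working it through.** **Step 1: the two statements side by side.** Patients are to be randomised according to stratified lists, yet each envelope is a random pick. An assignment cannot both follow an ordered list and be a free draw. What survives depends on how the envelopes are held:

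| Feature | One pooled stock | Separate set per age group |
|---|---|---|
| List order | lost | lost |
| Any blocking | lost | lost |
| Age stratification | lost | kept in full only if the set is used up |
| Assignment checkable against a due list position | no | no |

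**Step 2: size of the imbalance.** The protocol gives no figure to reproduce. Its only numerical input is enrolment of 100. The assumptions are 1:1 allocation, strata of 33, 33 and 34, and, for the comparator, permuted blocks of 4.

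Let a stratum of *n* patients draw at random from *N* envelopes, half per arm. The number *K* in one arm is hypergeometric, the imbalance is |2K − n|, and

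SD(2K − n) = √[n(N − n)/(N − 1)].

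For n = 33:

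- pooled, N = 100: √(33×67/99) = 4.73
- separate, N = 34: √(33×1/33) = 1.00
- separate, N = 40: √(33×7/39) = 2.43
- separate, N = 50: √(33×17/49) = 3.38
- separate, N = 60: √(33×27/59) = 3.89

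For separate sets the strata are independent. The chance that at least one is out by 6 or more is therefore 1 − (1 − p33)²(1 − p34), with exact hypergeometric tails:

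| Envelopes per set | p33 | p34 | Any stratum out by 6 or more |
|---|---|---|---|
| 34 | 0 | 0 | 0% |
| 40 | 0.0083 | 0.0202 | 3.6% |
| 50 | 0.0718 | 0.1284 | 24.9% |
| 60 | 0.1188 | 0.1923 | 37.3% |

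For one pooled stock of 50 and 50, the mean absolute imbalance is 3.8 patients per stratum. The chance that some stratum is out by 6 or more is 46%, and by 8 or more 24%. With strata of 20, 30 and 50 these chances become 50% and 27%. Simulation with 20,000 runs agrees to within about a percentage point.

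Comparator: with blocks of 4 opened in order, a stratum of 33 is eight full blocks plus one patient (imbalance 1), and a stratum of 34 is eight blocks plus two (imbalance 0 or 2). The maximum is 2.

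**Step 3: what the pooled imbalance does to the outcome.** Put the cited 7% in the youngest stratum and 14% in the other two. A mean imbalance of 3.8 patients with 50 per arm shifts the between-arm difference by 3.8/50 × 7 = 0.5 percentage points. Its direction is random.

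**Step 4: the age bands.** A series per stratum works only if every patient has exactly one stratum. Section 8 makes patients eligible from about 60, but the bands begin at 65, so ages 60 to 64 have no list. Age 70 falls in two bands.

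**The case against.** The envelopes are made from the stratified list, so the reading that respects both sentences is one set per age group. On that reading only the order within a stratum is lost, and if the sets hold few spares the balance is nearly intact. A reader might infer that the random pick throws away the stratification altogether. The text does not support that, because it does not say that the envelopes are pooled. The 46% belongs to the worst branch only.

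A reader might also infer that allocation was, or will be, steered, or that tampering could never be found. That too goes beyond the document. The envelopes are sealed and opened after eligibility and willingness are re-confirmed, and one blind draw from sealed envelopes is unpredictable. Steering would need an envelope to be opened and replaced, or to be see-through. The envelopes also carry codes, so used codes could be compared with the list afterwards. What is absent is a stated log or reconciliation, not the possibility of one.

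Finally, this is a pilot at one hospital with patients, informants and researchers blind, and chance imbalance in age adds noise that an age-adjusted analysis can reduce.

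All of this stands and limits the size of the point. It does not remove it. The random pick is a stated procedure that conflicts with the list, not a detail left for later, and a later analysis plan cannot restore concealment.

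**Conclusion.** The point holds in a limited form and should be fixed. The order of the list and any blocking are lost on any reading; the age stratification is lost only if the envelopes are pooled. The chance that some stratum is out by 6 or more runs from 0% (separate sets, almost fully used) through 4%, 25% and 37% (sets of 40, 50 and 60) to 46% (one pooled stock), against a maximum of 2 with blocks of 4 in order. These figures rest on assumed 1:1 allocation, assumed stratum and set sizes and an assumed block size, none of which the protocol gives.

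The imbalance is chance imbalance with a small effect on the outcome. The main weakness is that an unblinded clinician picks freely and no stated step would show an envelope reopened, swapped or discarded. That is a weakness in concealment and auditability, not evidence of bias.

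**What to change.** Delete "an envelope selected randomly by the anaesthetist" and put in its place, for example:

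> Sequentially numbered, opaque, sealed envelopes are prepared from the list, one series per age stratum, in permuted blocks of varying size. Within a series they are opened strictly in number order. Patient identifier, date and time are written on the envelope before it is opened. All used and unused envelopes are reconciled against the list. Where feasible, existing staff other than the treating anaesthetist hold the envelopes.

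Keep the existing rule that the envelope is opened only after eligibility is re-confirmed. Redefine the age strata so that they do not overlap and cover every eligible age from 60, so that each patient belongs to exactly one series.

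The cost is protocol wording, numbering of the envelopes and a simple log. No extra staff or patients are needed, but the change has to be in place before the first patient is randomised.
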